### Patient stratification (Aim 2b)

Within-disorder heterogeneity, common in EDs, has both research and clinical implications [71–75]. Data driven taxonomy has improved disorder classifications previously [76]. We will mirror recent work using PRS to derive genetic clusters of schizophrenia phenotypic subtypes [77, 78] and apply advanced, unsupervised machine learning to group samples for clinically relevant outcomes, and compare these with ED PRS clusters. Standard steps include variable selection and normalization, Uniform Manifold Approximation and Projection (UMAP) [79] for dimensional reduction, and visualization and identify subgroups with HDBSCAN [80] density-based clustering. To ensure robustness and reliability, the clustering algorithm will be validated by applying the same procedures to both training and replication datasets (e.g., applying the same clustering algorithm across sites). Cluster similarity will be evaluated to assess the consistency and reproducibility of the clusters. Validated novel patient clusters will be compared to standard DSM-5 diagnoses with agreement matrices to identify whether clusters better explain clinical outcomes and heterogeneity, as well as demonstrate genetic diversity.

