#### Aim 2: Apply statistical genetic analyses to better understand the heterogeneity and underlying biology of EDs

A multistage approach will implement a state-of-the-science pipeline for ED genomics. Primary analyses will include a GWAS of diagnoses, component behaviors, and dimensional traits, followed by case-case comparison, SNP-heritability (SNP-h^2^), genetic correlations (*r*_*g*_), polygenic risk scores (PRS), rare copy number variant (CNV) analyses, and bioinformatic integration for meaningful translation of GWAS results. Detailed phenotypes and PRS will be used for patient stratification, comparing standard diagnostic approaches with a novel, data-driven taxonomy of EDs. Finally, we will evaluate the hypothesis that AN is a "metabo-psychiatric disorder" by clarifying its relationship with metabolic and anthropometric traits through linkage disequilibrium score regression (LDSC), pathway-based PRS analysis (PRSet), phenome wide association study (PheWAS), Mendelian randomization (MR), and other emerging methods.

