### Risk prediction (Aim 3)

A key outstanding question in complex trait genetics is how individuals with high genetic risk remain resilient (i.e., disease-free), while others with low genetic risk may develop disease. Here, we will compare high ED-PRS cases to low ED-PRS cases, and high ED-PRS cases to high ED-PRS controls to characterize ED risk and protective factors and parse the ‘gene x environment’ relationship [9]. For case-case comparison, we will meta-analyze case samples from EDGI, EDGI2, UK Biobank, and other biobanks. Low PRS cases will be investigated for environmental contribution to disorder development in the absence of high genetic risk. We will perform PheWAS with the following comparisons: top decile vs. bottom decile cases, top decile vs. all other cases, and low decile vs. all other cases. As pathway risk aggregation can differ from genome wide PRS, we will also compare pathway-PRS in high and low PRS cases to identify pathways with notable contribution to genetic risk or resilience. Similarly, we will then compare high PRS cases to high PRS controls to identify potentially protective environmental and genetic factors against disorder development despite the presence of overall genetic risk.

Finally, we will repeat clustering analyses as described in *‘Patient Stratification (Aim 2b)’*, using PRS scores as clustering variables in place of phenotype clustering [103]. ED GWAS (ANGI, EDGI, EDGI2, and ARFID Genes and Environment [ARFID-GEN]) are combined for maximum sample size, and PRS will be calculated for ED behaviors, psychiatric co-morbidities, and metabolic traits for each sample. PRS curve is nonlinear (disproportionally greater in those with the greatest PRS burden [104–106]) and will thus be categorized into quartiles as ordinal variables, from which Gower distance matrices will be derived and used as input for clustering. Our primary analysis will be case-based clustering but will additionally expand to case–control and control-only clustering (controls: ≥ 30 years old, no lifetime ED symptoms) for a more robust investigation. Clusters will be compared for diagnostic and symptomatic prevalence, and we will repeat PheWAS as described for PRS decile comparisons above.

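### The Aim 2b cluster validation tests whether a UMAP–HDBSCAN partition is reproducible, not whether discrete patient groups exist

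*Protocol article*

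**What the plan says.** In the Protocol article, Patient stratification (Aim 2b), variables are chosen and normalized, and UMAP is then used "for dimensional reduction, and visualization and identify subgroups with HDBSCAN [80] density-based clustering". Dimension reduction is named apart from visualization, so the natural reading is that HDBSCAN works on the UMAP embedding.

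Two sentences define validation:
- "the clustering algorithm will be validated by applying the same procedures to both training and replication datasets", with running it across sites as the example;
- "Cluster similarity will be evaluated to assess the consistency and reproducibility of the clusters".

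Clusters that pass are then put to use: "Validated novel patient clusters will be compared to standard DSM-5 diagnoses with agreement matrices", in order "to identify whether clusters better explain clinical outcomes and heterogeneity, as well as demonstrate genetic diversity". The clusters are also to be compared with clusters built on polygenic risk scores (PRS). The Study aims section (Aim 2) names the intended product: "comparing standard diagnostic approaches with a novel, data-driven taxonomy of EDs".

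Risk prediction (Aim 3) returns to the method: "we will repeat clustering analyses as described in" Aim 2b. There the inputs are PRS cut into quartiles, with Gower distances, for cases and additionally for case–control and control-only sets.

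**The concern.** UMAP preserves local neighbourhoods rather than density, so it can break a continuous cloud into islands, and a density-based method reads islands as subgroups. If the second dataset shares the factor structure, skew and item formats of the first, the same procedure may cut it in similar places. Similarity between the two results then shows that the cut is reproducible. It does not show that there are separate kinds of patient.

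The later comparison with clinical outcomes does not close the gap. If severity is a continuum and outcomes worsen along it, any slicing by severity will be associated with outcomes.

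At stake is the word taxonomy. A severity gradient cut into pieces could pass the stated validation, be set against DSM-5 as a rival classification, and be carried into Aim 3. The GWAS results are not affected.

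**Working it through.** The article states no sample size, error rate or agreement figure for the clustering, so there is no figure to reproduce. The check is a simulation.

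**Inputs from the article.** The order of steps (normalize, UMAP, HDBSCAN) and the validation rule (same procedures on two datasets, then compare).

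**Inputs assumed.** 20 variables; n = 1,500 with 6 dataset pairs (12 datasets) per setting; UMAP in 2 dimensions with neighbours/minimum distance 15/0.1 and 30/0.0; HDBSCAN minimum cluster size 5, 1% of n (0.01 × 1,500 = 15) and 5% of n (0.05 × 1,500 = 75).

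**Populations.** Four without groups: independent Gaussian variables, two continuous factors, one skewed severity continuum, and one continuum seen through ordinal and binary items. A population with three real groups served as positive control.

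**Agreement.** Training labels were carried to the replication data by 15-nearest-neighbour classification in the original variables. They were compared with the labels found there independently, leaving out points HDBSCAN calls noise:

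ARI = (RI − E[RI]) / (max RI − E[RI]),

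where RI is the share of point pairs treated alike by both labelings. Chance agreement gives 0 and identity gives 1.

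**Results at n = 1,500**

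| Population | UMAP+HDBSCAN finds ≥2 clusters, min. size 5 or 15 | Same, min. size 75 | HDBSCAN without UMAP, min. size 15 or 75 | ARI at min. size 75: mean (largest pair) |
|---|---|---|---|---|
| Independent Gaussian | 100% | 0% | none | no clusters; 0.00–0.02 at settings that gave clusters |
| Two factors | 100% | 83–92% (10 or 11 of 12) | none | 0.36–0.49 (0.80) |
| Skewed severity | 100% | 100% | none | 0.52–0.69 (0.95) |
| Ordinal/binary items | 100% | 100% | 2 clusters | 0.63–0.70 (0.94) |
| Three real groups | 3 clusters every time | 3 clusters every time | 2 or 3; always 2 at size 75 | 1.00 |

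For the three continua at minimum size 75, training and replication gave the same number of clusters in 33–83% of pairs.

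**Larger samples.** With n = 3,500 (5 pairs; minimum size 35 or 175), mean ARI was 0.43–0.56 for skewed severity (largest 0.92) and 0.46–0.50 for ordinal items (largest 0.74). The other populations were not completed at this size.

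**Separate simulations.**
- Two-factor data without groups, n = 1,500, minimum size 75: 2 clusters in all 12 datasets, ARI 0.50–0.90. HDBSCAN on the unreduced variables found none in all 6 training sets.
- Fifteen three-factor scales without groups, n = 2,000–2,500: ARI 0.76–0.92 for skewed, floor-limited integer scores at minimum size 100 (3 runs), and 0.02–0.81 for Gaussian scores.

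**Aim 3 input.** Eight Gaussian scores (pairwise correlation 0.2, no groups, n = 1,500) were cut into quartiles and clustered with Manhattan distance, which is proportional to Gower here. UMAP+HDBSCAN gave 2–21 clusters in 16 of 16 datasets. At minimum size 75, both halves gave 2 clusters in 3 of 4 pairs, with ARI 0.48–0.59. HDBSCAN without UMAP gave 2–4 clusters in 15 of 16, so the quartile coding alone can produce clusters.

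**The case against.** The strongest reply is that the article does more than rerun an algorithm. It evaluates cluster similarity, and it compares the clusters with PRS clusters, DSM-5 diagnoses and clinical outcomes. A label-based similarity index exposed fragmentation of independent noise, and real groups gave ARI 1.00 against means of 0.36–0.70 for continua, so similarity does separate the two on average. This stands. It rules out the readings that the pipeline always finds clusters, that replication never catches an artefact, or that the planned taxonomy will be one. What remains is the overlap: single group-free pairs reached 0.95, and the validation described has no reference telling a reader what agreement a continuum alone would produce.

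A reader might also infer that UMAP is the culprit and should be replaced. The checks do not support that. Ordinal items and quartile coding gave clusters without UMAP, and HDBSCAN on the unreduced variables merged three real groups into two at minimum size 75.

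Sites differ in language, adaptation and recruitment, which makes agreement across sites harder than between two draws from one population. That is fair. Against it, the recruiting countries largely share one questionnaire battery (Table 1), so floors and item formats are largely common.

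Finally, tuning values and agreement thresholds may stand in a fuller document, and their absence here is no fault. The point concerns the validation the article does describe. A reproducible split of a continuum may still be useful for stratification, but it is not evidence of discrete kinds.

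**Conclusion.** The concern holds in limited form. Followed as described, the Aim 2b validation can pass a continuum with shared factor, skew or item-format structure as a set of validated clusters. Under the assumed settings, such continua were split in 83–100% of datasets at minimum cluster size 5% of n and n = 1,500. Train–replication agreement was often moderate to high (ARI about 0.4 to 0.95), though some Gaussian pairs fell near zero.

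The figures rest on assumed variables, sample sizes and settings, on 3 to 6 pairs per setting, and on an ARI that leaves out noise points. Those were 34–58% of points for the skewed and ordinal data at n = 1,500 and minimum size 75. The figures show that the failure is possible and not rare. They do not predict what the EDGI2 data will show. A named deliverable (Aim 2b) and part of Aim 3 are exposed.

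**What to change.** - Generate surrogate data from a single population with the same margins and correlations as the real variables, and run the whole pipeline on them, including the training and replication steps.
- Call clusters validated only if their number and their label-transfer agreement between training and replication data, taken together, exceed that reference distribution. Agreement should carry the main weight: at minimum size 1% of n, skewed group-free data gave a median of 8 to 8.5 clusters, while three real groups gave 3.
- Report clustering on the normalized variables or factor scores as a sensitivity analysis, not as a replacement for UMAP.
- Apply the same reference in Aim 3, with the surrogates cut into quartiles in the same way.
- If the reference is not exceeded, describe the result as a partition of a continuum rather than a taxonomy.

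The cost is a few sentences of analysis wording and computing time, with no new data. The downside is that fewer clusters, or none, may be declared.

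### Aim 2b names agreement matrices to decide whether clusters explain clinical outcomes better than DSM-5 diagnoses, but such a matrix contains no outcome and cannot decide this

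*Protocol article*

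**What the plan says.** The protocol article's Aim 2 sets the purpose: "Detailed phenotypes and PRS will be used for patient stratification, comparing standard diagnostic approaches with a novel, data-driven taxonomy of EDs".

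The section Patient stratification (Aim 2b) describes the method. The investigators will "apply advanced, unsupervised machine learning to group samples for clinically relevant outcomes, and compare these with ED PRS clusters". The steps are variable selection and normalization, UMAP for dimension reduction, and HDBSCAN for density-based clustering. The clustering is to be "validated by applying the same procedures to both training and replication datasets", for example across sites, and the similarity of the resulting clusters is assessed for consistency. Then comes the comparison with diagnosis: "Validated novel patient clusters will be compared to standard DSM-5 diagnoses with agreement matrices to identify whether clusters better explain clinical outcomes and heterogeneity". The same sentence also asks whether the clusters show genetic diversity.

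Risk prediction (Aim 3) repeats the clustering, "using PRS scores as clustering variables in place of phenotype clustering". This confirms that the Aim 2b inputs are phenotypes. The article does not list them.

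**The concern.** The plan asks a comparative question about a third variable: which of two labellings, cluster or DSM-5 diagnosis, better explains clinical outcomes? The tool it names for this looks only at the two labels. That is more than a detail left for an analysis plan, because a method is stated and it does not fit its question. Pathway specific PRS, written at the same level of condensation, does name a suitable kind of measure: variance explained, in a nested comparison.

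A second, conditional concern is that no outcome is set aside from the clustering. If the variables that form the clusters also serve to judge them, the clusters have an advantage that diagnosis does not have.

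At stake is whether EDGI2 could support or refute a statement that a data-driven taxonomy outperforms DSM-5. Such a statement would have clinical implications.

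**Working it through.** The article gives no figure for Aim 2b, so there is none to reproduce. All numbers below are illustrative assumptions.

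**1. What a matrix can show.** Take 4 diagnoses and 4 clusters, with 350 patients in each diagonal cell and 50 in each off-diagonal cell.

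- Each row and column total is 350 + 3 × 50 = 500, so N = 2,000.
- Observed agreement: 4 × 350 / 2,000 = 0.70.
- Chance agreement: 4 × (500 / 2,000)² = 0.25.
- Kappa = (0.70 − 0.25) / (1 − 0.25) = 0.60.

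Now add an outcome with residual variance 1 whose mean is 0, 1, 2 or 3 according to diagnosis.

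- Between-group variance of 0, 1, 2, 3 with equal groups: 1.25.
- R² for diagnosis = 1.25 / (1.25 + 1) = 0.56.
- Expected mean in cluster j (j = 0 to 3): 0.7j + 0.1(6 − j) = 0.6 + 0.6j. Its variance is 0.36 × 1.25 = 0.45.
- R² for clusters = 0.45 / 2.25 = 0.20.

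If the outcome means follow the cluster label instead, the matrix is unchanged and, by symmetry, the values swap: 0.20 for diagnosis and 0.56 for clusters. A simulation with 500 replicates gave 0.556 and 0.201 in the first case, and 0.200 and 0.557 in the second.

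The symmetry only makes the swap exact. For any matrix, if the outcome depends on one label alone, group means under the other label are averages of the first label's means. The other label can then explain no more, and it explains less wherever it mixes groups with different means. The matrix does not reveal which label the outcome depends on.

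**2. Whether another analysis fills the gap.** Within Aim 2b, the comparison with PRS clusters and the check on genetic diversity bring in other data, but neither concerns clinical outcomes. The prevalence comparison and PheWAS in Risk prediction (Aim 3) are stated for the PRS-based clusters. No passage describes a model of outcome on cluster versus diagnosis for the Aim 2b clusters.

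**3. Direction of the conditional problem.** Clusters gather patients who resemble one another on the input variables, so they tend to account for those variables well. A simulation checked the direction: 4,000 patients, 4 diagnostic groups as the only real structure, and k-means with 4 clusters standing in for the planned algorithm. The settings were 5, 10 or 20 variables with separation 0.5, and 10 variables with separation 1.0. On their own input variables the clusters had the higher R² in three of the four settings and were level in the fourth. On outcomes not used for clustering, diagnosis had the higher R² in all four. Only the direction is used here, because k-means is not the planned method.

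**4. What the planned validation covers.** Repeating the procedure in training and replication data tests whether the clusters recur. A stable cluster solution judged on its own inputs keeps the same advantage in every dataset.

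**The case against.** The best defence is that the sentence is condensed, that stratification is one component of Aim 2, and that the matrices are not the only evidence on the taxonomy. A matrix does describe how each diagnosis spreads across clusters, which bears on heterogeneity. All of that stands. None of it makes a cross-tabulation informative about clinical outcomes.

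The objection has more force against stronger readings that a reader might infer.

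- **That the clusters are certainly built from the outcomes used to judge them.** The wording "apply advanced, unsupervised machine learning to group samples for clinically relevant outcomes" could mean formed from such outcomes or formed with a view to them. Variable selection is named as a step, but the variables are not. A full protocol could reserve outcomes. The documents support only that, as written, none is set aside.
- **That the clusters would win even with no real subgroups.** The documents do not support this. The plan uses UMAP and HDBSCAN, and only validated clusters go forward. On 10,000 simulated patients with 5 or 10 independent variables, HDBSCAN (minimum cluster size 100) assigned nobody to a cluster. UMAP was not included in that run and could create apparent clusters. Four-cluster k-means solutions from pure noise agreed poorly between independent samples (mean adjusted Rand index 0.19, 0.09 and 0.04 for 5, 10 and 20 variables). They would probably fail a replication check, although the article states no threshold.
- **That the main result of Aim 2 is at risk.** Aim 2 names the GWAS and the genetic analyses that follow it as primary. The taxonomy comparison is an explicit part of Aim 2, but one part among several.

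**Conclusion.** The point holds in two parts of different strength. First, the named analysis cannot answer the Aim 2b question about clinical outcomes. This follows from what an agreement matrix contains and does not depend on simulation settings; the example shows one matrix compatible with 56% versus 20% in either direction. Second, and conditionally, if clustering inputs also serve as the yardstick, the comparison would tend to favour the clusters, and replication across sites would not correct it. No size can be put on this for EDGI2, since the inputs are not listed and the planned algorithm was not simulated in full. The plan should be changed, but the GWAS and the other genetic analyses are unaffected.

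**What to change.** Keep the agreement matrices as a description of overlap between clusters and diagnoses. For the comparison itself:

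- Name clinical outcomes that are not clustering inputs. Candidates already collected include ED-QOL, WHODAS (adults only) and ED treatment history in Table 1, and the Swedish register data in Case definitions.
- Derive the clusters in the training data and assign replication patients to them.
- In the replication data, compare diagnosis-only, cluster-only and combined models by out-of-sample R² or AUC, with confidence intervals.
- State how patients left unassigned by HDBSCAN are handled, so that all models are compared on the same patients.

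The cost is a paragraph of analysis wording, some extra modelling, and the loss of a few variables as clustering inputs. No new data are needed. Swedish individual-level data cannot be shared, according to the Analyses section, so any part that uses them would have to be run at that site.

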### Interrogating AN as a metabo-psychiatric trait hypothesis (Aim 2c)

#### Genetic correlations

We will replicate previously identified psychiatric, metabolic, and anthropometric correlations [3] using the EDGI2 cohort. We will follow the approach described in the primary analysis for *r*_*g*_. We will use the largest available GWAS data for heritable metabolic and anthropometric traits [81–90] at the time of the analysis and correct for multiple testing using FDR.

#### Pathway specific PRS

Pathway PRS is an extension of PRS that identifies how risk alleles aggregate in particular gene pathways and enables inference of mechanisms of genetic risk conferral. We will use PRSet [91] and established gene set repositories including GO, SynGO, KEGG, and REACTOME for cohort specific analysis, and validate findings against UK Biobank. We will perform single and multiple pathway associations within each ED and assess proportion of variance explained with a nested approach. All analyses will be corrected for ancestry PCs, age, and sex [92].

#### PheWAS

We will leverage existing UK Biobank data to test for relationships between clinical phenotypes and between ED-associated genetic variants and PRS. UK Biobank data include diet, medications, biochemical assays, exercise, substance use, anthropometry, and broad diagnostic histories. For each ED, PRS will be calculated for all participants in UK Biobank, and phenome-wide association studies (PheWAS) performed to test for associations between higher PRS and clinical and diagnostic data. QC of UK Biobank phenotypic data will include visualization of quantitative trait distribution, and tests for non-normality of distributions (heteroskedasticity). An FDR correction will be applied to correct for multiple testing. We will seek replication of significant findings in the All Of Us, Adolescent Brain Cognitive Development (ABCD), and PsychEMERGE cohorts [93].

